| **CRITERIA FOR EVALUATION**  **Efficacy :** Primary variable Time to occurrence of choroidal new vessels in the study eye  *(The following prognostic factors: age, history of addiction to smoking, total cholesterol and apoE genotype will be considered as well as fish intake frequency)*  **Main Secondary variable(s)**  Percentage of patients for whom new vessels occur during the study and  Change from baseline in:   - Visual acuity (ETDRS) - DHA concentration in red blood cell membrane - Drusen (number, size and area) - Retinal function (multi focal ERG)   **Safety :**   - Slit Lamp Examination results (including grading of lens opacification/LOCS II) - Fasting plasma lipoprotein profile - Adverse or unexpected events |

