## 6.2 Safety variables

### 6.2.1 Ocular tolerance

Objective ocular tolerance will be assessed in each eye at each visit, by an examination of the eye with the slit lamp. This examination will be performed without fluorescein or dye on each visit.

Slit lamp examination results will be recorded as normal or abnormal. Abnormalities will be described in the case report form. If any abnormality is noticed which was either not present at baseline or which is worse than at baseline, then the investigator will have to complete an adverse event form .

A precise evaluation of the lens opacity will be performed through the dilated pupil, using the LOCS II scale (appendix I.F).

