### 6.2.2 Systemic tolerance

Fasting plasma lipoproteins profile [triglycerides (TG), total cholesterol (TC), HDL-C and

LDL-C] will be performed on D0, at the 6 month visit and at the 3 year visit. To this end blood samples after fasting will be taken. The protocol for dosage is described in appendix I.D. If any abnormality is noticed which was either not present at baseline or which was worse than at baseline, then the investigator will have to complete an adverse event form .

Moreover, all systemic adverse events, particularly digestive adverse events (nausea, eructations, diarrhea or abdominal pain) and bleeding events*, will be registered all along the study (see paragraph 6.2.3).

** because there is no simple, specific and accurate biologic index allowing to predict the risk for bleeding.*

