At each follow-up visit, the percentage of patients with changes (from the previous assessment) in the slit lamp examination will be compared between groups by means of a CHI square test or a Fisher test .

Change from baseline in profile of plasma lipoproteins will be compared between groups using a Student t-test or a Wilcoxon Rank Sum test depending on data normality.

Adverse or unexpected events will be counted and described by visit. In case of a sufficient number of adverse events, the percentage of patients having at least one adverse event will be compared between the 2 groups by means of a CHI square test. In case of serious adverse events, these will be counted and described completely and the corresponding patient profile will be detailed.

Other variables

The comparability of quantitative parameters between groups on D0 will be analysed by a Student t-test or a Wilcoxon Rank sum test depending on data normality. Qualitative parameters will be analysed by a CHI square test or a Fisher test depending on the number of patients in classes.

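### The slit-lamp safety test counts undirected change since the previous visit instead of worsening from baseline, and the named bleeding and digestive events have no between-group comparison of their own

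*Protocol*

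**What the plan says.** **Slit lamp, analysis.** Under the safety variables of protocol section 8.1: "At each follow-up visit, the percentage of patients with changes (from the previous assessment) in the slit lamp examination will be compared". The test is chi-square or Fisher, and no direction of change is given.

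**Slit lamp, measurement.** Section 6.2.1 records each examination as normal or abnormal, with abnormalities described, and adds a LOCS II lens grading. It takes baseline as the reference: "If any abnormality is noticed which was either not present at baseline or which is worse than at baseline", an adverse event form is completed. The protocol summary puts the lens grades inside the safety variable: "Slit Lamp Examination results (including grading of lens opacification/LOCS II"). Section 8.1 gives them no comparison of their own.

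**Other longitudinal comparisons in section 8.1.** Visual acuity, multifocal ERG, drusen and plasma lipoproteins are all compared as change from baseline.

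**Adverse events.** Section 6.2.2 has all systemic events registered, "particularly digestive adverse events (nausea, eructations, diarrhea or abdominal pain) and bleeding events". In section 8.1, events are counted and described by visit and serious events are described in full. Only one between-group test is named: "the percentage of patients having at least one adverse event will be compared between the 2 groups by means of a CHI square test". It is also conditional ("In case of a sufficient number of adverse events"), and how many events would be sufficient is not stated. Section 8.1 also provides for individual listings of all data.

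**The concern.** Section 3 makes confirming safety a stated purpose, over three years of treatment. The natural ocular question is whether more patients on one arm end up with eyes worse than when they started. The slit-lamp test answers a different question: in how many patients did something differ, for better or worse, between two consecutive visits. If onset is gradual, the difference between arms is split over four visit intervals. If onset is early, it appears once and then drops out of the comparison.

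The adverse event test has a related weakness. All events count, whatever their cause (section 6.2.3). An excess of one specific type is therefore diluted by patients who would have had some other event anyway.

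At stake is how a finding of no difference between groups would be read. It could be taken as reassurance on cumulative ocular worsening or on bleeding when the tests had little chance of showing either.

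**Working it through.** The protocol gives no safety event rates and no power figure for safety, so there is no stated figure to reproduce. All rates below are assumptions, used to show direction and rough size.

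**Step 1. What the two definitions count**

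| Course of a finding | Section 8.1: change since previous visit | Worsening from baseline |
|---|---|---|
| New at Month 6, persists | Month 6 only; none at Years 1, 2, 3 | Month 6 and Years 1, 2, 3 |
| Present at baseline, gone at Year 1, stays gone | Year 1 | Never |
| New at Month 6, gone at Year 1 | Month 6 and Year 1 | Month 6 only |

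The first row under-counts a lasting harm. The second counts an improvement alongside harms.

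**Step 2. Slit lamp, illustrative power**

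Inputs: two-sided 5% test; section 8.2 gives 124 per group and 20% drop-out, so 124 × 0.80 = 99 per arm. Assumed: 20% v 10% worsened by Year 3, persisting, one third of onsets in each year, hence 6.7% v 3.3% in the last interval.

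Power = Φ[(d − 1.96·SE0)/SE1], with SE0 = √(2p̄(1−p̄)/n) and SE1 = √([p1(1−p1)+p2(1−p2)]/n).

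- From baseline at Year 3: d = 0.10, p̄ = 0.15, SE0 = 0.05075, SE1 = 0.05025. (0.10 − 0.09947)/0.05025 = 0.0105, power **50.4%**.
- Since previous visit at Year 3: d = 0.0333, p̄ = 0.05, SE0 = 0.03098, SE1 = 0.03089. (0.0333 − 0.0607)/0.03089 = −0.887, power **18.8%**.
- With 124 per arm: 60% and 22%.

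**Step 3. Other assumed patterns, 124 per arm**

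- Persisting onset of 5% v 10% per interval over the four intervals. Last interval: 0.05 × 0.95³ = 4.3% v 0.10 × 0.90³ = 7.3%, power 17%. From baseline: 1 − 0.95⁴ = 18.5% v 1 − 0.90⁴ = 34.4%, power 81%.
- Onset of 4% v 8% per interval: 16% against 72%.
- All onset by Month 6, 5% v 15%: the Month 6 test has 75% power. At Years 1 to 3 the measure shows no change in either arm.

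**Step 4. Allowing for the tests at earlier visits**

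Simulating the step 2 scenario with three yearly tests, at least one is significant about 44% of the time, against 51% for the single cumulative test. The three tests together have a false-positive rate of about 12%, against 5%.

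**Step 5. Any adverse event against a named event**

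Assume bleeding in 10% v 4%, independent of other events, and a share b of each arm with some other event. The any-event difference is (1 − b)(0.10 − 0.04). Power is for 99 per arm.

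| b | Any-event difference | Power, any event | Power, bleeding itself |
|---|---|---|---|
| 90% | 0.6 points | 3% | 38% |
| 70% | 1.8 points | 5% | 38% |
| 50% | 3.0 points | 6% | 38% |
| 30% | 4.2 points | 9% | 38% |

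Values below 5% arise because the formula counts only significance in the direction of the true difference. With other assumed rates (2% v 8%, 2% v 10%, 5% v 15%; b from 30% to 90%; 124 per arm), the any-event test has about 4% to 21% power. A test on the named event has 58% to 76% (chi-square) or 47% to 70% (Fisher).

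**The case against.** A reader might infer that persisting ocular worsening, bleeding and digestive events would be missed. The protocol does not support that. A slit-lamp finding that is new or worse than at baseline goes on an adverse event form. Bleeding and digestive events are registered throughout, events are counted and described by visit, serious events are described in full, and all data are listed. What is lacking is a between-group comparison, not detection.

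Four further objections deserve weight.

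- **The two sections can coexist.** Section 6.2.1 sets a reporting trigger and section 8.1 a per-visit comparison; both can be carried out as written. This stands: it is a mismatch of reference point, not a strict contradiction.
- **Tables by event type commonly sit in an analysis plan,** which is not at hand. This stands and makes the adverse event part secondary. It does not rescue the slit-lamp rule, which the protocol itself fixes.
- **The any-event percentage need not be near its ceiling.** The protocol gives no rate, and the condition on a sufficient number of events suggests that its authors did not count on saturation. This stands. A 90% background is one extreme, and the range in step 5 should be read instead. The dilution remains at 30%.
- **The Year 3 contrast picks the least favourable visit.** This stands in part. Across three yearly tests the loss of power is much smaller (44% against 51%), but that power comes with more false positives, and none of the tests estimates cumulative worsening.

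Nor are all the safety comparisons affected: lipoproteins are compared from baseline.

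**Conclusion.** The point holds for the slit-lamp rule. As written, it measures the wrong quantity: it has no direction, shifts its reference at each visit, and leaves cumulative 3-year worsening and the LOCS II grades without a comparison. It departs from section 6.2.1 and from the acuity, ERG, drusen and lipoprotein comparisons, and no reason is given. This conclusion follows from the definitions and needs no assumed rate.

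The size does rest on assumptions. At 99 per arm, with 20% v 10% worsening spread evenly by year, power is about 50% from baseline against about 19% in the last interval, with the gap narrowing once earlier visits are counted. Even the better measure is not strongly powered, which is a reason to report an estimate with an interval and not only a test.

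The adverse event point is secondary: bleeding and digestive events are under-compared. The dilution figures assume independence from other events and a background of 30% to 90%.

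The primary efficacy analysis is unaffected. The change should be made because safety is a stated purpose and the remedy needs no new data.

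**What to change.** 1. In section 8.1, replace the slit-lamp measure by the percentage of patients with worsening from baseline at each follow-up visit. Define worsening as in section 6.2.1 ("which was either not present at baseline or which is worse than at baseline") and include worsening of the LOCS II lens grade. Report the between-group difference with a 95% confidence interval.
2. Alongside the any-event comparison, report by arm the percentage of patients with at least one bleeding event and with at least one digestive event, each with risk difference and 95% confidence interval. Do not make these two summaries depend on an undefined number of events.

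Cost: a change of analysis wording and a few extra tables. The slit-lamp findings, LOCS II grades and adverse events are already collected, so no added visit, examination or patient is needed.

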## 8.2 Determination of sample size

The primary criterion is the time to occurrence of choroidal new vessels (CNV) in the study eye.

The occurrence rates of CNV in both treatment groups will be compared using a log-rank test.

According to previous studies (24) the 3 year risk of developing CNV in one eye is about 30 % (10% per year) for patients with CNV in the fellow eye.

Based upon expectation that DHA-treatment should reduce this rate to 15% at 3 years after D0 , sample size was thus performed assuming a 3 year CNV risk for the study eye in the treated group and in the placebo group to be 15% and 30% respectively.

The number of patients has been calculated with the Pass software for survival curves according to the following hypotheses:

- 2 tailed test
- Type I error  = 0.05
- Type II error  = 0.20 (80% power)
- Regular recruitment and Inclusion period: 1 year
- Follow up period per patient : 3 years
- Equal proportion of patients in each treatment group
- Drop-out rate in each group : 20%

Based on the above specifications the total number of patients should be 245.

Data on 248 evaluable patients are to be available (124 per group).

# 9. PATIENT FOLLOW-UP

## 9.1 Protocol deviation

The reason for deviations (inclusion errors, failure to comply with protocol ...), will be specified in all cases.

Assessments will continue until the end of the study unless the patient's condition requires to discontinue the study.

## 9.2 Premature withdrawal from the study

If a patient does not attend the scheduled control visit, he/she should be contacted again. In case of withdrawal, the reasons will be sought.

Generally, patients may withdraw or be withdrawn from the study for the following reasons:

- of their own free will
- if the investigator considers that the patient's health is compromised by remaining in the study
- if the patient is not sufficiently co-operative
- if a serious adverse event prevents the patient from attending the follow-up visits.

For any premature withdrawal, the investigator must give the date and the reason, and if possible provide an assessment of the therapeutic response.

# 10. ADMINISTRATIVE ASPECTS

## 10.1 Duration of the study

The inclusion period will be 12 months.

The scheduled study duration for each patient will be 3 years.

So the total duration of the study will be 4 years.

## 10.2 Confidentiality - Publication

All information concerning the product and the study is considered to be confidential and should not be disclosed to persons not involved in the study.

The results may only be published after mutual agreement between the sponsor and the investigator.

## 10.3 Contract

A contract will be drawn between the investigator and the sponsor stating the legal and financial aspects involved throughout the study.

# APPENDICES

**APPENDIX I. DESCRIPTION OF STUDY PROCEDURES**

A BEST CORRECTED VISUAL ACUITY

B FUNDUS PHOTOGRAPHY

C FLUORESCEIN AND INDOCYANINE GREEN ANGIOGRAPHY

D BIOLOGICAL ANALYSES

E APO E GENOTYPING

F LENS OPACITY CLASSIFICATION SYSTEM (LOCS II)

G MULTIFOCAL ERG

**APPENDIX II. PATIENT INFORMATION AND CONSENT FORMS**

GENERAL STUDY

GENETIC STUDY

**APPENDIX III. ADMINISTRATIVE DOCUMENTS**

APPROVAL OF THE CCPPRB

INSURANCE CERTIFICATE

**APPENDIX IV. JUSTIFICATION OF LAWFUL REGULARITY OF THE STUDIED PRODUCT**

# APPENDIX I. DESCRIPTION OF STUDY PROCEDURES

### I.A BEST CORRECTED VISUAL ACUITY

**(adapted from AREDS Manual of Operations)**

1. Visual Acuity Equipment and Facilities
   1. Introduction. The visual acuity of participants will be measured according to the standard procedure developed for the Early Treatment Diabetic Retinopathy Study (ETDRS) and adapted for the Age-Related Eye Disease Study (AREDS). The procedure is described in this section. The following equipment is used: a set of three Lighthouse Distance Visual Acuity Test charts (second edition), which are modified ETDRS Charts 1, 2, and R, and a retroilluminated box providing standardized chart illumination, as modified from the design by Ferris and Sperduto. The charts and boxes are manufactured by:

Lighthouse Low Vision Products

[name]

[name]

Telephone: + 1 [contact]

**Visual acuity testing is required at a distance of 4 meters and, for participants with sufficiently reduced vision, at 1 meter. The 4­-meter distance should be marked clearly and permanently; the 1-meter distance must be measured, with a 1-meter stick, with the participant in a chair (Section 1.5).**

- 1. Visual acuity charts. Charts 1 and 2 are used for testing the right and left eye, respectively, and Chart R is used for refraction. The features of the charts are five high-contrast Sloan letters in each of 14 lines, lines of equal difficulty, and a geometric progression of letter size (and, thus, an arithmetic progression of the logarithm of minimum angle of resolution) from line to line. Charts 1, 2, and R have different letter sequences. Participants should be prevented from seeing Charts 1 and 2 until refraction has been completed and the visual acuity test begins.

1.3 Visual acuity box. The dimensions of the light box are 24 and 3/4 inches by 25 and 3/4 inches by 7 inches. The box can be mounted on a wall or on a cylindrical stand manufactured by Lighthouse Low Vision Products. The stand is mounted on a five-pronged wheel base, with each prong about l4 inches long; two of the five wheels are lockable. When the box is mounted on the stand, its height can be varied.

The light box should be mounted at a height such that the top of the third row of letters (0.8 logMAR) is 49 2 inches from the floor.

The rear of the box provides storage space for the two charts not being used.

1.4 Illumination. Most of the room lights should be turned off during the visual acuity test. The box itself provides sufficient illumination for the examiner to record the test results. Additional light can have an adverse effect. With the box light off, not more than 15 footcandles of light should fall on the center of the chart.

The visual acuity light box is equipped with two General Electric Cool Daylight 20-watt fluorescent tubes and a ballast. Because the illumination of fluorescent tubes diminishes by 5 percent during the first 100 hours and by another 5 percent during the next 2,000 hours,

- New tubes should be kept "on" for about 4 days (96 hours, does not have to be continuous), and
- All tubes should be replaced once a year.

The fluorescent tubes should also be checked periodically for proper functioning. Replacement tubes can be purchased at a local store or from Lighthouse Low Vision Products.

Each tube is partly covered by a 14-inch fenestrated sleeve, open in the back, which serves as a baffle to reduce illumination. Each sleeve should be centered on the tube such that an equal length of tube (4 and 3/16 inches) is left uncovered to the right and left of the sleeve. The openings in the backs of the sleeves should be oriented to point directly toward the back of the box (i.e., the sleeves should not be tilted up or down). Also, the lower sleeve has a cutout that should point down toward the ballast.

1.5 Four- and 1-meter visual acuity lanes. A distance of exactly 4 meters (13 feet and 1.5 inches, or 157.5 inches) is required between the participant's eyes and the visual acuity chart for the 4-meter test, and a distance of exactly 1 meter (39 and 3/8 inches) is required for the 1-meter test.

The room for visual acuity testing must have, in addition to the 4-­meter lane, space for the visual acuity box (and possibly a stand) and space for the participant. Minimum room-length requirements vary according to how the box is mounted and whether the participant sits in a chair or stands for the 4-meter test.

- Wall-mounted box: In addition to the 4-meter lane, 7 inches must be allowed for the depth of the box plus space for the participant to sit or stand.
- Stand-mounted box: In addition to the 4-meter lane, 13 inches must be allowed for two of the stand's casters to touch the rear wall (or a line marked on the floor when there is no wall) plus space for the participant to sit or stand.

Marking the distance

4 meters

1. If the chair and visual acuity box are permanently affixed, distance measurements need to be made only once and no floor marks are needed to ensure the correct distance.
2. If the box is mounted on the wall but the participant's chair is not permanently affixed, the 4-meter distance of the participant's eye from the chart must be marked clearly and permanently.
3. If the box is mounted on a movable stand, the 4-meter distance must be marked clearly and permanently on the floor. The location and orientation of the box must be rechecked each time a new chart is put in place or the box is touched. When the stand touches the rear wall of the room, two of the five casters should touch the wall.

1 meter

The 1-meter distance is measured from the eye of the participant, seated comfortably in a chair with his or her back firmly placed against the chair's back, to the center of the second or fourth letter of the third line of the chart, using a 1-meter stick. The stick may be homemade (e.g., a dowel rod) or purchased at a local hardware store or by mail (e.g., from Johnson Level and Tool Manufacturing Company, Inc., Mequon, Wisconsin).

2. Testing Best-Corrected Visual Acuity

2.1 **Four-meter test**. **TESTING OF ALL EYES BEGINS AT 4 METERS**. First, the right eye is tested with Chart 1 and then the left eye is tested with Chart 2. Each chart should remain hidden from view until the eye in question is ready for testing.

The distance from the participant's eyes to the visual acuity chart must be exactly 4.0 meters (13 feet and 1.5 inches, or 157.5 inches). The participant may stand or sit for the 4-meter visual acuity test. If the participant is seated, his or her back should fit firmly against the back of the chair. The examiner should ensure that the participant is standing or sitting comfortably, that the head does not move forward or backward during the test, and that the participant's eyes remain at the 4-meter distance.

The testing procedure for visual acuity is based on the principle that the objective is to test visual acuity and not intelligence or the ability to concentrate or follow or remember instructions (although all of these factors are involved). The participant should be told that the chart has letters only and no numbers. If the participant forgets this instruction and reads a number, he or she should be reminded that the chart contains no numbers and the examiner should request a letter in lieu of the number.

The participant should be asked to read slowly (at a rate not faster than about one letter per second) in order to achieve the best identification of each letter and to not proceed until the participant has given a definite response. It may be useful for the examiner to demonstrate the letter-a-second pace by reciting "A, B, C, . . . ." If, at any point, the participant reads quickly, he or she should be asked to stop and read slowly. If the participant loses his or her place in reading or the examiner loses his or her place (possibly because the letters are read too quickly), the examiner should ask the participant to go back to where the place was lost. Examiners should never point to the chart or to specific letters on the chart or read any of the letters during the test.

Each letter is scored as right or wrong (Section 2.3). Once a participant has identified a letter with a definite single-letter response and has read the next letter, a correction of the previous letter cannot be accepted. If the participant changes a response aloud (e.g., "That was a 'C,’ not an 'O’.”) before he or she has read aloud the next letter, then the change should be accepted. If the participant changes a response after beginning to read the next letter, the change is not accepted.

When the participant says he or she cannot read a letter, he or she should be encouraged to guess. If the participant identifies a letter as one of two or more letters, he or she should be asked to choose one letter and, if necessary, to guess even if the next letter has already been read. The examiner may suggest that the participant turn or shake his or her head in any manner if this improves visual acuity. If the participant does this, care must be taken to ensure that the fellow eye remains covered. When it becomes evident that no further meaningful readings can be made, despite urgings to read or guess, the examiner should stop the test for that eye.

There are several reasons for encouraging participants to guess: (1) participants' statements that they cannot identify a letter are often unreliable; (2) encouraging them to guess helps to maximize the participant's effort; (3) it helps to assure

uniformity among procedures performed by different investigators.

2.2 **One-meter test**. Eyes reading 19 or fewer letters correctly at 4 meters should be tested at 1 meter. If the trial frame is to be removed when changing the test distance from 4 meters to 1 meter, the testing chart (Chart 1 or 2) should first be removed from view to prevent the participant from reading the chart with the fellow eye.

Before testing at 1 meter, a +0.75 sphere should be added to the 4­-meter correction already in the trial frame to compensate for the closer testing distance. The participant may stand or sit for the 4-meter test, but must sit for the 1-meter test. (As indicated in Sections 1.5 and 3.1, the participant should be seated comfortably with his or her back firmly placed against the back of the chair.) The avoidance of any head movement forward or backward is particularly important during the 1-meter test. The participant should be asked to read only the first six lines at 1 meter, making 30 the maximum score attainable at that distance (Section 2.3).

After the test of the right eye is completed, occlude the right eye and replace Chart 1 by Chart 2. The test isrepeated for the left eye, starting at 4 meters. When testing of the left eye is completed, Chart 2 should be removed from view; Chart R may be mounted in preparation for the next participant.

2.3 Scoring best-corrected visual acuity. The examiner records each letter identified correctly by circling the corresponding letter on the Visual Acuity Worksheet. Letters read incorrectly and letters for which no guesses are made are not marked on the form. Each letter read correctly is scored as, one point. The score for each line (which is zero if no letters are read correctly) and the total score for each eye are recorded on the Visual Acuity Worksheet after testing is completed. If testing at 1 meter is not required, 30 points are automatically scored for the 1-meter test. The total combined score (i.e., the sum of the 4- and 1-meter scores) and the approximate Snellen fraction, which is determined based on the lowest line read, are recorded on the Visual Acuity Worksheet and on the appropriate Case Report Form.

Exhibit 1, taken from Ferris et al, lists visual acuity in various units of measurement equivalent to the acuity represented by the expected number of letters identified correctly on the ETDRS or Lighthouse charts.

- 1. Light Perception and no light perception. If visual acuity is so poor that the participant cannot read any of the largest letters at 1 meter (i.e., the number of letters read correctly at 1 meter is zero), light perception should be tested with an indirect ophthalmoscope in a darkened room. The indirect ophthalmoscope light

should be in focus at 3 feet with the rheostat set at maximum voltage. From a distance of 3 feet, the beam should be directed in and out of the eye at least four times, and the participant should be asked to respond when he or she sees the light. If the examiner is convinced that the participant perceives the light, vision should be recorded as "light perception"; if not, vision should be recorded as "no light perception."

- 1. Legal blindness. Assessing legal blindness (20/200 or worse) with the visual acuity charts used in this study may present a problem. On standard Snellen charts, the line below 20/200 is 20/100, and so the usual definition of legal blindness (20/200 or worse) could be reworded "worse than 20/100.” The ETDRS charts, however, contain two lines, 20/160 and 20/125, between the 20/200 and 20/100 lines, and so a participant, who should be considered legally blind, may actually read better than 20/200 but worse than 20/100 when tested on the ETDRS charts. This may prevent participants from being designated legally blind, depriving them of economic and social benefits. It is, therefore, suggested that legal blindness be assessed with standard Snellen acuity charts.

